### Quantitative component

#### Organisational, teamwork and individual context

To document contextual factors (Obj. 1 & 3), the organisational context of the clinic will be assessed using the complete Model Maturity Matrix and the Model for Understanding Success in Quality (MUSIQ) based on the observations of the research team with the collaboration of the clinic’s manager [86, 87]. Then, a self-reported survey composed of a total of 45 items adapted from several questionnaires will be used. Teamwork context will be assessed using the mean score of the Team Climate Inventory short-form (TCI) (19 items) [88, 89]. Job satisfaction will be measured using the Mini Z Burnout Survey (10 items) [90, 91]. Work engagement (3 items) will be measured using the Copenhagen Psychosocial Questionnaire (COPSOQ) [92]. Team composition will be expressed by the number and types of providers working at the clinic, and team stability will be measured by the length of time each team member has been in the clinic as well as the stability of the team throughout the length of the project. To assess the individual context, the Improvement Readiness scale of the SCORE survey [93, 94] (5 items) as well as the agree subscale of the Quality improvement commitment instrument (8 items) will be used [95, 96]. The overall questionnaire should take around 10 to 15 min to complete.

#### AA structural change & processes (Obj. 2)

Each team member will complete the “*Outil Réflexif Accès Adapté*” (ORAA) questionnaire, which provides a comprehensive portrait of the participant’s adherence to each AA pillar [18]. Two versions of the questionnaire are available online in both French and English, one for PHC providers (39 items) and one for administrative staff (25 items), and take approximately 12 min and 6 min to complete, respectively. Each respondent is given a unique identifier to ensure confidentiality through a double validation process. Upon completing the questionnaire, respondents receive a personalised report and suggestions to improve their AA practice. Modifications to AA change packages will also be thoroughly documented as the project evolves.

#### AA Outcomes

Six key AA measures (see Table 1) will be extracted on a weekly or monthly basis via the EMR (Obj. 3). This has been accomplished with great success by the Quebec team over the last two years. Most of these indicators have been used in previous Quebec CQI initiatives on AA. These outcomes will be used to evaluate the effectiveness of the intervention and inform the PDSA cycles (among other indicators chosen by the clinics to document their PDSA cycles). We have successfully automated extraction of the six indicators from an EMR in Quebec. A scale-up process to the other EMRs is ongoing and will be finalised upon trial launch.

To assess effectiveness from patients’ perspectives (Obj. 3), patient-reported experiences will be assessed at each clinic using a 50-item online survey. The questionnaire has been developed based on comparable tools [80, 97–100] and recommendations from our patient committee. The 50 items cover various dimensions of access from a patient perspective, such as the appointment process, communication and team collaboration. The survey is available in French and English and takes approximately 11 min to complete. An electronic informed consent form precedes the survey. The survey will be distributed electronically to all registered patients for whom an email address is available (estimated between 40 and 80% depending on the clinic). This data collection strategy is inexpensive and includes friendly reminders. Both the questionnaire and distribution mode has been tested with success by the Quebec research team. Cognitive testing [101] has been used with eight patients to validate the tool.

### Qualitative component

Document analysis and non-participant observations [102–104] will be collected to document and compare structural organisational changes and processes of care with respect to AA (Obj. 2). All documents produced by the teams (e.g. PDSA cycle journaling, change packages) and all meeting minutes related to the three activities of the intervention will be summarised per clinic by the QI coaches using a coding grid. In addition, a logbook will be completed each week to document completed tasks and time spent on them. Every 3 months, QI coaches will evaluate the progress of each clinic for which they are responsible using the Assessment Scale for Collaboratives [105].

At the end of the intervention (T18), as well as 12 months after the intervention (T30), we will conduct focus groups with purposefully selected members of the QI teams to document their ongoing perspectives on CQI processes, their appreciation of CQI methods and the perceived impact on their practice (Obj. 1). Implementation issues and the need for additional training or educational tools will be discussed. With the intervention group, we plan to conduct an average of 10–12 interviews at three times (T12, T18, T30) to better understand the level of appreciation for QI and barriers and facilitators to engaging in QI activities. We will interview a variety of professions and roles within the clinic to ensure information-rich discussions [106].

### Data analyses

For the first objective, the analysis will be based on the InQuIRe framework (Fig. 2). Audio recordings and transcripts of interviews will be reviewed simultaneously, to assess validity of the transcription process, and analysed using an iterative approach [107, 108]. Thus, the analysis process will progress as follows throughout data collection for each site: 1) development of a mixed deductive-inductive classification grid; 2) coding according to the classification grid of an initial interview; 3) discussion and team consensus on the final grid; 4) linking of the various emerging themes; 5) coding of all interviews; and 6) validation by two judges (counter-coding) of at least 20% of the material in order to validate the classification. Data saturation will be determined as defined by Constantinou et al. [109] This will be followed by an inter-site analysis to identify commonalities between and specificities of the sites examined [110] and to compare the different configurations between sites [111]. Data will be analysed by wave first. Finally, matrices based on waves will be generated to identify particular intra- and inter-wave patterns [112].

Strategies used to instill structural changes in the organisation and processes of care (Obj. 2) will be rigorously documented and categorised by AA pillar. During PDSA cycles of a given strategy, its efficacy within each clinic will be assessed using run charts [113] and control charts [114] and their respective rules of interpretation. In addition to distinguishing systematic changes from chance variation [115], these types of graphs will allow for monitoring of the performance of the strategy developed by the clinics to improve AA and inform the PDSA cycles (Activity 2 of the intervention).

The impact of the intervention on AA outcomes (Obj. 3) will be structured around the quintuple aim [116]. For all outcomes, we will describe clinics and participants using means and standard deviations or medians and interquartile ranges. Also, time series analyses will be performed based on EMR indicators to detect changes since baseline, at the beginning of the intervention (T3), during the intervention (T3–T18) and the sustainability of the changes (T30). *Care team functioning*: To account for clustering of providers within clinics, the primary outcome measure, 3rd next available appointment, will be analysed using a generalised linear mixed model (with log link and quasi-Poisson distribution) adjusting for time to account for secular trends as well as important contextual factors such as number of providers and readiness for change. We will inspect missing data, and if more than 10% of the sample has missing values, we will use multiple imputation techniques. Otherwise, the maximum-likelihood method of estimation is considered adequate to address missing data in such regression models [117, 118]. Differences between the control and intervention periods and time trends will be estimated using odds ratios and their 95% confidence intervals. Similar regression models will be used (as dictated by the distribution of the data) to assess differences in % of 48-h open slots, walk-in usage, relational continuity and multidisciplinary involvement. *Patient experience*: A comprehensive description of patients’ experiences will be generated three times over the study. Items that focus on ease of access, perception of interprofessional collaboration, satisfaction with the appointment process and consultations outside the clinic for non-urgent care will be used for longitudinal analysis purposes. *Population health*: Discontinuity for chronic patients will be analysed using a generalised linear mixed model to assess the impact of the project on the management of chronic patients. *Health equity and inclusion*: Accessibility and patient experience will be stratified by visible minority status, ethnicity, preferred language, gender and physical or mental ability. If any disparity seems apparent, this issue will be addressed during the improvement efforts. *Efficiency:* Total costs to the system related to the implementation of the intervention as well as costs per clinic and cohort, accounting for different organisational characteristics, will be calculated. We will analyse the QI coach’s logbook to assign costs to the different tasks performed. Incremental ratios (i.e. change in costs to use the intervention divided by change in the 3rd next available appointment) will also be calculated.

The AA process and outcomes of the intervention (Obj. 4) will be documented 12 months after the end of the intervention to assess the sustainability of its effects over time. Regression models similar to those used in objective 3 will be used to identify the factors that influence sustainability of the intervention effects. Factors such as team context, participation in each intervention activity, support duration (wave) and progress made during the intervention will be included in the model. The association between the sustainability of outcomes and each factor will be estimated using regression estimates and their 95% confidence intervals. We will also evaluate whether the practices put in place (processes) are maintained.

In addition to the analyses described above, one interim analysis will be conducted after 12 months of the intervention. This analysis will focus mainly on the trial’s primary outcome (3rd next available appointment) to identify early evidence of the intervention’s superiority. This study will be monitored by an independent Data Safety and Monitoring Committee (DSMC) formed by the steering committee. The DSMB will consist of an independent healthcare organization expert, a PHC physician and a statistician who are not involved in this study. The interim analysis will be performed by a statistician who is blind to the treatment allocation. Members of the DSMC will also be responsible for developing terms of reference, including stopping rules to be used during interim analysis. The steering committee will be notified by the DSMC only if the latter considers continuance of the study to be futile.

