**Outcome**	
3rd next available appointment (weekly)	Number of days before the 3rd next available appointment open for general consultation
Relational continuity (monthly)	Total number of medical consultations with a patient’s attached family physician (or specialised nurse) out of the total number of consultations with any family physician (or specialised nurse) from the clinic. Evaluates relational continuity between the provider and their registered patients

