**Process**	
48-h capacity (weekly)	Proportion of appointments available in the next 48 h. Provides an overview of the provider’s ability to respond to urgent care demands
Use of walk-in clinics (monthly)	Proportion of consultations with registered patients offered through walk-in visits out of the total number of consultations with their attached professional
Professional diversity of care (monthly)	Proportion of consultations with a physician, resident or specialised nurse out of the total number of consultations with any provider at the clinic. Evaluates the level of involvement of different types of providers (social workers, nurses, pharmacists, etc.) with registered patients
14-day capacity (weekly)	Proportion of appointments available in the next 14 days. Provides an overview of the provider’s ability to respond to routine care and follow-up demands

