**Balancing**	
Discontinued care for patients with chronic disease (monthly)	Proportion of registered patients with at least one chronic condition who have not consulted the clinic within the last 12 months

The proposed CQI intervention present in Fig. 3 consists of three activities carried out iteratively until the improvement objectives are achieved or up to a maximum of 18 months of intervention: 1) team reflection and prioritisation of change needs; 2) PDSA cycles; and 3) group mentoring.

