### Data collection

Complementary qualitative and quantitative data will be collected over a period of 24 months. To evaluate the proposed trial objectives, data collection will be extended by 12 months *in the intervention group only*. We will collect data from all clinics in the intervention group for at least 3 months prior to the start of the intervention.

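### The four monthly EMR indicators have about three baseline points per clinic at the stated minimum, too few to estimate a prior trend; this matters most for the T30 series, which has no untreated comparator

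*Protocol article*

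**What the plan says.** Table 1 of the protocol article sets how often each EMR measure is extracted. Four are monthly: "Relational continuity (monthly"), "Use of walk-in clinics (monthly"), "Professional diversity of care (monthly") and "Discontinued care for patients with chronic disease (monthly"). Three are weekly: 48-h capacity, 14-day capacity and the primary outcome, "3rd next available appointment (weekly"). The text under AA Outcomes speaks of six measures although the table lists seven, so it is not fully fixed which monthly measures are meant.

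Data collection requires data from intervention clinics "for at least 3 months prior to the start of the intervention". It gives no baseline length for control clinics. The same section sets 24 months of collection and adds 12 months in the intervention group only. The opening of Methods says that control clinics will be offered the intervention 12 to 18 months after recruitment.

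Under Objective 3, Data analyses says that "time series analyses will be performed based on EMR indicators to detect changes since baseline, at the beginning of the intervention (T3"), from T3 to T18, and at T30 for sustainability. Beside the time series, it plans time-adjusted mixed or similar regression models for the primary outcome and for the monthly indicators.

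**The concern.** A time series detects a change by comparing what is observed with what the earlier series would have led one to expect. If a monthly indicator was already drifting, or its baseline fell in an unusual season, three earlier values cannot show it. The drift could then be reported as an intervention effect, or could hide one.

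While untreated control clinics are observed, they show any drift shared by both arms. They do not settle whether the two arms were already on different paths. That is a live question here: whole health regions are allocated, clinics volunteer, and matching is on clinic level rather than on earlier trend.

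At T30 even this protection is gone. The extended follow-up is in the intervention group only, and controls will by then have been offered the intervention. A statement that a change in continuity or chronic-care follow-up was sustained beyond what would have happened anyway then rests on the short pre-period alone.

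**Working it through.** The plan gives no number of pre-intervention points and no precision for the time series, so there is no figure of its own to reproduce.

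**Inputs from the article.** Measurement frequency (Table 1); minimum baseline of 3 months, 24 months of collection, and 12 more in the intervention group only (Data collection); intervention from T3, landmarks T18 and T30 (Data analyses); 24 clinics per arm (Sample size justification).

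**Assumptions for illustration.** Straight-line pre-trend; independent residuals with constant SD; independent clinics; the same baseline length in controls. Standard errors (SEs) are in residual SDs of one clinic-level observation.

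**1. Count of points.** Monthly: 3 × 1 = 3 before T3, and 15 from T3 to T18. Weekly: about 13 before T3.

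**2. Estimating the prior trend.** Residual df = n − 2; slope SE = 1/√Sxx.
- Monthly, months 1 to 3: Sxx = 2, SE = 0.71 per month, 1 df (97.5% t value 12.7).
- Weekly, weeks 1 to 13: Sxx = 182, SE = 0.074 per week, or 0.074 × 52/12 = 0.32 per month, 11 df (t value 2.20).

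Three months cover 3 of 12 calendar months, so season cannot be estimated at all.

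**3. Projecting the no-intervention level in one clinic.** SE = √(1/n + (t − x̄)²/Sxx).

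| Monthly baseline | x̄ | Sxx | Month 18 | Month 30 |
|---|---|---|---|---|
| 3 points (months 1 to 3) | 2 | 2 | √(1/3 + 16²/2) = 11.3 | √(1/3 + 28²/2) = 19.8 |
| 15 points (months −11 to 3) | −4 | 280 | √(1/15 + 22²/280) = 1.34 | √(1/15 + 34²/280) = 2.05 |

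With a serial correlation of 0.3, the 3-point SE for the effect at month 18 is 10.7 instead of 11.3, so the result does not hinge on independence. The weekly series gives about 5.3 at month 18, in SDs of a weekly value: less affected, but not immune.

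**4. Adding month-of-year terms to the 15 points.** There are 13 parameters and 2 residual df. The slope comes from three pairs of months 12 apart, with variance (2/12²)/3 = 0.00463. Months 18 and 30 share a calendar month with month −6, so the SEs are √(1 + 24² × 0.00463) = 1.9 and √(1 + 36² × 0.00463) = 2.6. The gain is smaller than in step 3. With 3 points this model cannot be fitted.

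**5. Pooling the 24 intervention clinics at month 30, without controls.** 19.8/√24 = 4.0 with 3 points; 2.05/√24 = 0.42 with 15; 2.6/√24 = 0.53 with 15 and month-of-year terms.

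**6. Comparison of 24 with 24 up to T18.**
- Difference-in-differences of period means, prior trends taken as equal: √(1/3 + 1/15) × √(2/24) = 0.18. With 15 baseline points: √(1/15 + 1/15) × √(2/24) = 0.11.
- Each arm given its own pre-trend (effect at T18 from a segmented regression): 11.34 × √(2/24) = 3.27. With 15 baseline points, the one-clinic SE is √(1.34² + 1/15 + 7²/280) = 1.43, giving 1.43 × √(2/24) = 0.41.

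**7. Discontinued care.** It counts chronic patients "who have not consulted the clinic within the last 12 months". Successive monthly values share 11 of 12 months of look-back, so three values carry less information than the formulas assume. A value dated 12 months before T0 needs records from 24 months before T0.

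**The case against.** The strongest reply is that the effect estimates come from elsewhere. The time series are an additional analysis. The monthly indicators also have regression models, and 24 concurrent control clinics remove drift common to both arms, with an SE of 0.18 at the minimum baseline. This stands: a reader might infer that the short baseline undermines the effectiveness comparison or the primary outcome, and the documents do not support that. The primary outcome is weekly and has its own time-adjusted model.

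The article also does not specify a straight line for each clinic carried forward to month 30. Whether the series are per clinic, pooled or controlled is detail that an article may leave to the full plan. So the SEs in residual SDs are illustrations, not properties of a stated model. Three months is a floor, and if waves start at different times of year, the baseline seasons would differ between clinics.

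A reader might further infer that the clinic-level control charts will give frequent false signals. Individuals charts with limits frozen on three points would do so in about 40% of stable series over 15 months (simulation, independent normal data). But the article fixes neither the chart type nor how limits are set, and it uses the charts to guide improvement cycles. Proportion charts with an assumed 500 or 1,500 consultations a month and no overdispersion give about 12%. No finding rests on this.

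What the reply does not meet is T30. The article itself plans to read sustainability from these series at a time when it collects no control data. Nor can three points per clinic check the equal prior trends on which the 0.18 depends.

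**Conclusion.** The point holds for the four monthly indicators (or those of them that are among the six measures in the text). At the stated minimum, about three pre-intervention points per clinic cannot support an estimate of prior trend or season, or a check that the arms were on similar paths. The consequence is limited up to T18, as long as untreated controls are observed, and greatest at T30. There the pooled projection for 24 clinics has an illustrative SE of about 4.0 residual SDs, against 0.42 with 15 points, or 0.53 with month-of-year terms as well. These sizes rest on a straight-line pre-trend with independent residuals and independent clinics. The count of points and the absence of a T30 comparator come directly from the article. Weekly indicators are affected less, and the controlled regression comparison remains usable.

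**What to change.** In Data collection, state that the consultation-based monthly indicators will be extracted retrospectively for at least 12 months before T0, in both arms, wherever the EMR holds the needed history. For discontinued care this means 24 months of records. State the same baseline length for control clinics.

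In Data analyses, state that these indicators will be analysed as a controlled interrupted series through the controlled period, and say when that period ends, given that controls may start the intervention 12 to 18 months after recruitment.

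Where the history cannot be rebuilt, for example because past attachment status is not kept, limit trend-adjusted time-series conclusions to the weekly indicators. Report the monthly ones as controlled comparisons while controls are observed, and as descriptive change at T30.

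The cost is a longer EMR query, data-quality checks on older records and a few sentences of wording. No extra clinics or visits are needed. Feasibility is an inference from the 12-month look-back that one indicator already requires. It must be confirmed for each EMR, because the article reports automated extraction from one system, with scale-up to the others under way.

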### Sample size justification

The Quebec CQI pilot project showed that the average time to the 3rd next available appointment (primary outcome) is 11 days (sd = 10). Forty-eight clinics (clusters) averaging 15 professionals per clinic for a total of 720 professionals over six measurement time points will be measured every week or month (depending on the measure). An assumed intracluster correlation (ICC) of 0.364 (from the pilot project) provides about 80% power to detect a small effect size of 0.25 (Cohen’s d, assuming that variation will increase over the course of the intervention). This translates into a 50% reduction in time to the 3rd next available appointment from the baseline assessment [83]. Variations in clinic size have been considered (coefficient of variation of 0.49 according to the pilot project) [84]. No inflation for loss to follow-up is planned because the data is readily obtained from the EMR system for all professionals. Provision for one interim analysis 12-months post recruitment is planned using the Demets and Lan’s alpha spending function approach [85]. Thus, we aim to recruit 48 PHC clinics (24 interventions and 24 controls) for the trial proposed in this study.

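### The primary model is quasi-Poisson, which has no full likelihood, yet the plan relies on maximum likelihood to cover missing data at 10% or less

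*Protocol article*

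**What the plan says.** Under Data analyses, the primary outcome is to be fitted with a "generalised linear mixed model (with log link and quasi-Poisson distribution"), adjusted for time and for contextual factors such as number of providers and readiness for change. The reason given for a mixed model is clustering: "To account for clustering of providers within clinics, the primary outcome measure, 3rd next available appointment".

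The missing-data rule has two branches. Above the threshold, "if more than 10% of the sample has missing values, we will use multiple imputation techniques". At or below it, "Otherwise, the maximum-likelihood method of estimation is considered adequate to address missing data in such regression models".

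Sample size justification expects few gaps: "No inflation for loss to follow-up is planned because the data is readily obtained from the EMR system for all professionals". Table 1 lists the outcome as "3rd next available appointment (weekly"), while the sample size paragraph describes "Forty-eight clinics (clusters) averaging 15 professionals per clinic for a total of 720 professionals over six measurement time points". Data analyses then compares control with intervention periods and estimates time trends. It also plans separate time series analyses of the record-based indicators. The random effects are not listed.

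**The concern.** Maximum likelihood gives valid estimates under missing at random because the full distribution of the observed data, including each unit's own earlier values, enters the likelihood. Quasi-Poisson does not supply that distribution. It states that the variance is proportional to the mean and estimates the proportionality factor. The plan therefore credits its primary model with a property that the model does not have.

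The affected branch is the one the plan expects to use, since near-complete data are anticipated. If missing weeks depend on earlier observed waits, for instance because busier clinics or later-connected record systems have more gaps, the only stated safeguard does not apply as described.

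A related matter is worth settling in the same edit. The outcome repeats weekly on the same providers and the contrasts are between periods, so the standard errors depend on how correlation over time is modelled.

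**Working it through.** **1. The two statements side by side.**
- Model: log link, quasi-Poisson. What is specified is E(Y) = μ and Var(Y) = φμ, with no probability distribution when φ differs from 1. A mixed model of this kind is fitted by quasi-likelihood, for example penalised quasi-likelihood.
- Missing-data rule at 10% or less: validity is attributed to maximum likelihood.

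The second needs a likelihood and the first does not provide one. Both concern the same primary analysis in the same paragraph, so a separate analysis plan could not make both true; one has to change. There is no figure in the plan to reproduce here, and the stated power does not depend on this point.

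**2. How much could it matter?** The plan gives a mean of 11 days and SD 10. Write p1 and p0 for the missing fractions in the two arms, and δ for the difference between unseen and seen waits. The bias in the arm difference, before any correction by the model, is (p1 − p0) × δ. With equal arms and 10% missing overall, p1 + p0 = 0.20. The splits and δ below are assumptions.

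| Missing, arm 1 / arm 0 | δ = 5 days (0.5 SD) | δ = 10 days (1 SD) |
|---|---|---|
| 10% / 10% | 0 | 0 |
| 15% / 5% | 0.10 × 5 = 0.5 day | 0.10 × 10 = 1.0 day |
| 20% / 0% (extreme) | 0.20 × 5 = 1.0 day | 0.20 × 10 = 2.0 days |
| 3% / 1% (2% overall) | 0.02 × 5 = 0.1 day | 0.02 × 10 = 0.2 day |

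For scale, the target effect is 0.5 × 11 = 5.5 days if read as the 50% reduction, or 0.25 × 10 = 2.5 days if read as d = 0.25 at the baseline SD. These are bounds on all missing-data bias. Maximum likelihood would remove only the part predictable from observed values.

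**3. What unmodelled correlation over time could do (illustration only).** Inputs from the plan: 24 clinics per arm, 15 providers, ICC 0.364. Assumed: total variance 1, 13 weeks before and 65 after in both arms, clinic autocorrelation between periods c = 0.90, and a model with a clinic intercept alone.
- Weeks factor: 1/13 + 1/65 = 0.0923.
- Clinic-by-period variance: 0.364 × (1 − 0.90) = 0.0364. Residual: 1 − 0.364 = 0.636.
- Model SE of the pre-post arm contrast: √[(2/24) × ((0.636 + 0.0364)/15) × 0.0923] = 0.0186.
- True SE if each clinic's deviation stays constant within a period: √[(2/24) × (2 × 0.0364 + (0.636/15) × 0.0923)] = 0.080.
- Type I error of a nominal 5% test: 2 × [1 − Φ(1.96 × 0.0186/0.080)] ≈ 65%.
- True SE if the clinic deviation is redrawn every week: √[(2/24) × (0.0364 + 0.636/15) × 0.0923] = 0.0246, giving about 14%.
- With six time points (1 before, 5 after) the same two cases give about 20% and 14%. With c = 1, all return to 5%.

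A null simulation on six time points (3 before, 3 after) shows the same dependence on unstated quantities. Ignoring only a persistent provider effect (variance share 0.3 to 0.5) makes the pre-post test conservative, at about 0–1%. With a provider share of 0.3, also ignoring a clinic-by-period share of 0.02, 0.05 or 0.10 gives about 5%, 12% or 25%. A between-group level contrast keeps about 5–6% throughout.

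**The case against.** The likelihood point can be called loose wording. Quasi-likelihood estimates stay valid when missingness depends only on modelled covariates such as time or clinic size; the gap concerns missingness that depends on observed outcomes. A penalised quasi-likelihood fit still uses random effects, so a provider's observed weeks carry some information about the missing ones. Above 10%, multiple imputation is already planned, and the data come from routine records. All of this stands, and it is why the effect is rated small. It does not remove the contradiction: the approximate protection of such a fit is not the property that the plan cites. Some gaps are also possible, since the AA Outcomes section says automated extraction works in one record system and is still being extended to the others.

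On correlation over time, the objection is stronger. A quasi-Poisson mixed model can carry provider and clinic-by-period effects, so nothing about the repeats follows from the choice of distribution. A condensed article commonly leaves the random-effects list to the analysis plan. This stands in full.

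**Conclusion.** The plan is wrong as written on one point: the stated primary model lacks the likelihood on which its missing-data rule at 10% or less depends. That conclusion needs no assumption beyond the text. The consequence is probably minor. On the assumptions above, the bias is 0.1 to 0.2 days at 2% missing with a 3%/1% split, and reaches 1 to 2 days only when missingness is at the threshold and falls in one arm alone.

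A reader might go further and infer that clinic is the only clustering level, that weekly values are treated as independent, and that the primary test would therefore reject far too often. The article does not support this. It gives a reason for using a mixed model, does not list or limit the random effects, and plans separate time series analyses. The 65% figure rests on an assumed autocorrelation, a clinic deviation held constant for 65 weeks, and 13 baseline weeks in both arms. Data collection states at least 3 months of pre-intervention data for the intervention group only. Other equally open assumptions give 14%, 5% or less than 1%. The correlation structure is thus something to confirm before analysis.

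**What to change.** Choose one of two routes and state it in Data analyses.
1. Replace quasi-Poisson with a log-link count mixed model that has a likelihood, negative binomial or Poisson-lognormal, fitted by maximum likelihood. The existing missing-data sentence then becomes true under missing at random.
2. Keep quasi-Poisson, delete the maximum-likelihood sentence, and use multiple imputation that respects the clinic and provider levels below 10% missing as well as above it.

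Under either route, list the random effects. For weekly data and between-period contrasts these should include provider and clinic-by-period terms as well as clinic. If the full analysis plan already specifies them, a cross-reference is enough.

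The cost is wording plus a longer model fit, with monthly averaging of the weekly values as a pre-stated fallback if the model does not converge. No new data or clinics are needed. The change should precede the 12-month interim analysis, which focuses on the same primary outcome.
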